#### Secondary therapeutic outcomes

5.1.2

TCM syndrome score scale;WAB;Water swallow test;MoCA;GAP-43;MAP-2.

### Therapeutic mechanism outcomes

5.2

#### Criterion of primary therapeutic outcomes

5.2.1

1.The comparison of obvious effective rate and effective rate in improvement degree of motor function and living ability among groups and within groups.2.The comparison of before-and-after treatment in fMRI of the brain in the resting state.

*Applying Nimodipine methods*:Clinical control rate: n ≥ 90%Obvious effective rate: 90% > n ≥ 70%Effective rate: 70% > n ≥ 30%Ineffective rate: n < 30%n = [(points before treatment − points after treatment) ÷ points before treatment] × 100%, n is expressed as a percentage.

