### Grouping

2.3

According to previous studies, the effective rate of the routine treatment group is 80 percent and the morbidity rate of eye-acupuncture and routine treatment group is 90 percent. Suppose *α* is 0.05 (one side) and *β* is 0.20. Calculated by PASS 11, the sample size in both groups is 157. With an estimated 10 percent dropout rate, the sample size is 175. Thus 360 patients will be recruited and divided into 2 groups in the study, with half of them (n = 180) in the control group (routine treatment group) and others (n = 180) in the experimental group (eye-acupuncture combined with routine treatment group).

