#### Criterion of secondary therapeutic evaluation index/criterion of secondary therapeutic outcomes

5.2.2

1.Activity of daily living (ADL) scales (modified Barthel index); WAB; water swallow test; MoCA; GAP-43; MAP-2.2.The quantified and classified standard for TCM symptoms*Effectivity*: the symptoms and signs in TCM improve and the score n ≥ 50%;*Inefficiency*: the symptoms and signs in TCM do not obviously improve, or even become worse, and the score n < 50%.n = [(total score before treatment − total score after treatment) ÷ total score before treatment] × 100%.3.The comparison of obvious effective rate and effective rate among groups and within groups made by ADL scales (modified Barthel index), WAB and water swallow test; the comparison of before-and-after treatment in GAP-43 and MAP-2.

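### Response rates are to be compared within groups as well as between them, but on no available reading can a within-group comparison of these rates show an effect of eye-acupuncture

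*Protocol article*

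**What the plan says.** Section 5.2.1 of the protocol article, item 1, sets as a primary criterion "The comparison of obvious effective rate and effective rate in improvement degree of motor function and living ability among groups and within groups". The rates come from a per-patient percentage change, "n = [(points before treatment − points after treatment) ÷ points before treatment] × 100" (per cent), cut into bands. The lowest band that counts as a response is "Effective rate: 70% > n ≥ 30" (per cent). Below it lies "Ineffective rate: n < 30" (per cent). Section 5.2.2, item 3, uses the same construction for secondary outcomes: "The comparison of obvious effective rate and effective rate among groups and within groups made by ADL scales", together with the aphasia battery and the water swallow test.

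No within-group test is named, and no pair of time points is given for the rates. Section 5.4 schedules the primary outcomes on the first day, Day 14 and Day 28. Section 5.6 adds a telephone Barthel assessment four weeks after treatment.

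The sample size in section 2.3 uses only a contrast between the arms: "the effective rate of the routine treatment group is 80 percent", against 90% with eye-acupuncture (printed as a morbidity rate), at a one-sided alpha of 0.05 and 80% power.

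**The concern.** A response rate built from change already contains the before-and-after comparison. Comparing such a rate within an arm either repeats that comparison against a baseline at which nobody can be a responder, or follows the rate over time in one arm. In both cases natural recovery and routine rehabilitation count in full.

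That matters in this trial. Patients enter within three months of onset (section 3.3), both arms receive rehabilitation training (section 4.3), and section 5.5 says there is no blinding. Improvement is expected without eye-acupuncture. A report that the rate rose significantly within the experimental arm would be read by many as support for the treatment, although the same statement would very probably be true of the control arm. Because the within-group comparison is written into the outcome criteria, such a report would follow the plan.

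**Working it through.** **1. The plan's own figure.** Inputs from section 2.3: rates 0.80 and 0.90, one-sided alpha 0.05 (z = 1.645), power 0.80 (z = 0.842). With pooled variance and no continuity correction:

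n = [1.645 × √(2 × 0.85 × 0.15) + 0.842 × √(0.80 × 0.20 + 0.90 × 0.10)]² ÷ 0.10² = (0.831 + 0.421)² ÷ 0.01 ≈ 157 per group.

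Allowing for 10% dropout: 157 ÷ 0.90 = 174.4, rounded up to 175. Both stated figures reproduce, and 180 per arm are planned. The calculation is a between-group one, and no within-group comparison enters it.

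**2. First reading: before v after.** Setting the after score equal to the before score in the formula gives n = 0% for every patient. Since 0% is below 30%, every patient is ineffective at baseline, so the before rate is 0/180 in each arm. This does not depend on the sign of n. In a paired table all discordant pairs then run one way, and with b responders:

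- exact McNemar, one-sided: p = 0.5^b; b = 4 gives 0.0625, b = 5 gives 0.031
- exact McNemar, two-sided: p = 2 × 0.5^b; b = 5 gives 0.0625, b = 6 gives 0.031
- McNemar chi-square, uncorrected: statistic = b; b = 4 gives p = 0.0455
- McNemar chi-square, continuity-corrected: statistic = (b − 1)² ÷ b; b = 5 gives 0.074, b = 6 gives 0.041
- Fisher's test of 0/180 v b/180, as an unpaired variant, two-sided: b = 5 gives 0.061, b = 6 gives 0.030

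The threshold is therefore 4 to 6 responders, or 2.2% to 3.3% of 180. The tests are assumptions, because the article names none.

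**3. How easily an arm passes.** Take the highest threshold, 6 of 180. If the 80% of section 2.3 is this response, 0.80 × 180 = 144 control patients respond and P(at least 6) = 1.000. With 90%, 162 respond and the probability is again 1.000. If a single band holds far fewer patients, P(at least 6) is still 0.9998 at a true rate of 10% and 0.89 at 5%.

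**4. Second reading: Day 14 v Day 28.** Both rates use the same baseline score and the first need not be zero, so the structural problem disappears. What remains is whether more patients cross a threshold by Day 28 than by Day 14 in one arm. There is no concurrent comparator, so recovery and routine care cannot be separated from eye-acupuncture. For Barthel, a comparison with the later telephone assessment has the same limit.

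**The case against.** The strongest reply is that the article never states a before-versus-after test of rates. The formula needs a post-treatment score, so a pre-treatment rate is not defined in the plan, and 0/180 is a consequence the reader has to draw. Where the authors mean before versus after they say so, for resting-state fMRI and for the two proteins; for the rates they use a different phrase. Two post-baseline visits make Day 14 v Day 28 a coherent description, and the choice of test may be left to an analysis plan that is not shown. All of this stands. It means that the p-values above belong to one reading and cannot be presented as what the plan prescribes. It does not rescue the comparison as an efficacy criterion, because the other reading is uncontrolled.

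Three stronger claims are tempting, and the documents do not support them. A reader might infer that the plan gives the within-group and between-group comparisons equal standing. They share a sentence, but no ranking is stated, the design is a parallel controlled trial, and only the between-group contrast is powered. A reader might also claim that measurement error alone would make the within-group result significant. That depends on the error of the scales and the distribution of baseline scores, neither of which the article gives. Finally, a reader might treat 80% as the plan's forecast for this exact response. Section 2.3 does not say which scale or band its effective rate means, and section 5.2.1 keeps the bands separate, so the near certainty in the control arm is conditional.

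As printed, n is negative when a score that rises with improvement goes up. That is a separate matter; responder here means improvement in the intended direction.

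**Conclusion.** The point holds in a limited form. Sections 5.2.1 and 5.2.2 place a within-group comparison of response rates among the outcome criteria, and neither available reading lets it show an effect of eye-acupuncture. Read as before versus after, it is met by 4 to 6 responders out of 180, and in the control arm with near certainty if the 80% refers to this response. Read as Day 14 versus Day 28, it describes time course only. The first result assumes 180 analysed patients per arm and one of the tests listed; the second needs no numerical assumption.

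The trial's valid comparison is unaffected, since it appears in the same sentence and is the one the sample size supports. The wording should be corrected before analysis, because as it stands it allows an uncontrolled improvement in an unblinded trial to be reported as meeting a criterion of efficacy.

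**What to change.** In section 5.2.1 item 1 and section 5.2.2 item 3, delete the within-group part of the comparison of response rates. Alternatively, keep it, name the time points, and label it descriptive with no significance test. Add one sentence saying that the efficacy conclusion rests on the between-group difference in rates, the contrast on which section 2.3 bases the sample size.

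The cost is two short wording changes and one added sentence. No new data, visits or patients are needed, the sample size stands, and nothing in clinical management changes. All that is lost is a comparison that cannot separate the treatment from recovery.

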#### Primary therapeutic outcomes

5.1.1

ADL scales (modified Barthel index);Simple Fugl–Meyer motor function score;Functional magnetic resonance imaging (fMRI) of the brain in the resting state.

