#### Visit 1 (Day-3∼0)

5.4.1

The basic demographic information, past medical and treatment history, course of the disease, complication, medication, and so on.General vital signs: temperature, respiration, heart rate, and blood pressure (measured after sitting still for 5 minutes).General physical examination and specialist examination.Laboratory examination: blood routine examination (red blood cell count, white blood cell count, platelet count, hemoglobin), urine routine examination, 4 coagulation tests (prothrombin time, activated partial thromboplastin time, plasma fibrinogen, and thrombin time), and 12-lead ECG examination.fMRI of the brain in the resting state and GAP-43 and MAP-2.Primary and secondary outcomes scale evaluation.Qualified patients (meeting all inclusion criteria and failing to meet all exclusion criteria) are randomly divided into groups based on the random number and they are informed of the treatment method.After the first treatment, the experimental group has an fMRI of the brain in the resting state.

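### The stated criterion for resting-state fMRI (primary) and for GAP-43 and MAP-2 (secondary) is before-and-after change and names no between-arm contrast

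*Protocol article*

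**What the plan says.** Section 5.1.1 lists "Functional magnetic resonance imaging (fMRI) of the brain in the resting state" as one of three primary outcomes. Section 5.1.2 gives the secondary outcomes as "TCM syndrome score scale;WAB;Water swallow test;MoCA;GAP-43;MAP-2".

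Section 5.2.1 sets the criterion for the primary outcomes in two items. Item 1 compares effective rates in "improvement degree of motor function and living ability among groups and within groups". Item 2, for fMRI, reads in full "The comparison of before-and-after treatment in fMRI of the brain in the resting state".

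Section 5.2.2, item 3, has the same split within one sentence. It opens with "The comparison of obvious effective rate and effective rate among groups and within groups made by ADL scales", extends this to the WAB and the water swallow test, and closes with "the comparison of before-and-after treatment in GAP-43 and MAP-2".

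On data collection, Visit 1 (section 5.4.1) lists "fMRI of the brain in the resting state and GAP-43 and MAP-2" with no restriction to one arm, and Visit 4 on Day 28 (section 5.4.3) lists the same measurements, again with no restriction. Visit 1 also contains an extra scan: "After the first treatment, the experimental group has an fMRI of the brain in the resting state".

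**The concern.** The trial randomises so that eye-acupuncture plus routine treatment can be compared with routine treatment alone. A before-after comparison inside an arm does not use that randomisation. Patients enter within 3 months of onset (section 3.3), and both arms receive basic treatment and rehabilitation training (section 4.3), so both may well change over four weeks whether or not eye-acupuncture adds anything. Repeat measurement can add a shift of its own.

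A significant change in the experimental arm would therefore not show that eye-acupuncture works. Nor would significance in one arm and not in the other, because that is not a test of the difference between them. At stake is what may be claimed from a primary outcome in a trial without blinding (section 5.5).

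The scan after the first treatment raises a separate and smaller matter. With no matching control scan, an immediate effect of needling cannot be told apart from the effect of being scanned a second time or of the first rehabilitation session.

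**Working it through.** **1. What the plan's own calculation rests on.** Section 2.3 assumes effective rates of 80% and 90%, one-sided α = 0.05 and β = 0.20. With pooled variance and no continuity correction:

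n = [1.645·√(2·0.85·0.15) + 0.842·√(0.8·0.2 + 0.9·0.1)]² / 0.10² = (0.831 + 0.421)² / 0.01 ≈ 157 per arm.

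This matches the stated 157, and 157 / 0.9 = 174.4 gives the stated 175. The trial is thus sized on a between-group difference in effective rates. The calculation does not cover fMRI or the biomarkers.

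**2. The criteria side by side.**

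| Outcome | Status | Comparison named |
|---|---|---|
| Motor function, living ability | primary | between and within groups (5.2.1, item 1) |
| Resting-state fMRI | primary | before and after (5.2.1, item 2) |
| ADL, WAB, water swallow test | listed in 5.2.2 | between and within groups (5.2.2, item 3) |
| GAP-43, MAP-2 | secondary | before and after (5.2.2, item 3) |

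The between-group comparison is named twice, and twice the adjoining text uses a different formula for the imaging and biomarker outcomes.

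**3. How often a before-after test is significant with no treatment effect.** Inputs:
- Analysed per arm: 180 × 0.9 = 162 (180 per arm and 10% dropout, section 2.3).
- Test: two-sided 5%, critical value 1.96 (assumed).
- Shared change d, in SDs of the change score and equal in both arms (assumed, because the article gives no mean or SD for these outcomes).
- Each outcome is treated as a single continuous measure, with a normal approximation.

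P(significant) = Φ(d√162 − 1.96) + Φ(−d√162 − 1.96), with √162 = 12.73. The second term is negligible except at or near d = 0.

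| d | d√162 | d√162 − 1.96 | P(experimental arm significant) |
|---|---|---|---|
| 0 | 0 | −1.96 | 5% |
| 0.1 | 1.27 | −0.69 | about 25% |
| 0.2 | 2.55 | 0.59 | 72% |
| 0.25 | 3.18 | 1.22 | 89% |
| 0.3 | 3.82 | 1.86 | 97% |
| 0.5 | 6.36 | 4.40 | over 99.9% |

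A between-arm test of change stays at 5% in every row, because the shared change cancels.

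**4. Significant in the experimental arm but not in control.** With independent arms this probability is p(1 − p), where p is the last column above. It is 0.247 × 0.753 = 19% at d = 0.1 and 0.889 × 0.111 = 10% at d = 0.25, and it is close to zero at d = 0.5. Its maximum is 25%, reached where p = 0.5, that is at d = 1.96 / 12.73 = 0.154.

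**The case against.** The strongest reply is that the text excludes nothing. Item 2 of section 5.2.1 names no test and does not say within-arm. It may simply name the quantity, change, that will be compared between arms. The abstract speaks of change from Visit 1 to Visit 4 for every outcome in a parallel controlled trial, and measuring fMRI and biomarkers without arm restriction would serve little purpose if the control arm were then ignored. The lists are also loose: MoCA is given no comparison at all, and the TCM syndrome score has a responder threshold but no named contrast. Choice of model is ordinarily left to the analysis plan.

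Much of this stands. A reader might infer that the plan rules out a between-arm comparison, and the document does not support that. The reply does not remove the point, however, because the plan has not left the matter open. It states a criterion for a primary outcome, and that criterion differs from the one next to it, where the groups are expressly compared. An analysis plan that followed the wording literally would test within-arm change.

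A reader might also infer that the extra scan lets natural recovery pass for a treatment effect. It does not: it follows the first treatment, so weeks of recovery do not bear on it. Section 5.4 does not list it among the primary outcome times, and the article attaches no efficacy claim to it. Its only defect is the missing comparator.

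It is fair, too, that baseline and centre adjustment is one reasonable choice among several, and that an fMRI analysis needs a defined measure. Any analysis of fMRI needs that, including the before-after one.

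**Conclusion.** The point holds for the stated criterion: for one primary outcome and two secondary outcomes it is before-and-after change, and taken literally it cannot separate eye-acupuncture from what both arms share. It needs correcting because fMRI is primary. For GAP-43 and MAP-2 alone it would weigh less. The other two primary outcomes and the sample size already rest on between-group comparison and are not touched by this point.

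The size is illustrative. At assumed shared changes of 0.1, 0.25 and 0.5 SD of the change score, a before-after test in the experimental arm is significant in about 25%, 89% and over 99.9% of trials with no treatment effect, against 5% for the between-arm test. These are not estimates of this trial's error rate, since the documents give nothing from which the shared change could be estimated. Nor should the 25% for significance in the experimental arm alone be read as typical, because it is the largest value that probability can take. What does not depend on the assumed figure is the direction: any shared change raises the before-after rate above 5% and leaves the between-arm rate where it is.

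**What to change.** In section 5.2.1, item 2, and in the GAP-43 and MAP-2 clause of section 5.2.2, item 3, make the criterion the between-arm difference in change from Visit 1 to Day 28 (Visit 4). Preferably estimate it as the difference in the Day-28 value adjusted for the Visit 1 value and centre. Keep the before-after results within each arm as description.

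In section 5.4.1, label the experimental-arm scan after the first treatment as descriptive.

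The cost is a change of wording in three places. The Visit 1 and Visit 4 measurements are already scheduled without arm restriction, so no new data, visits or participants are needed. If a between-arm comparison was always intended, the amendment only says so.

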### Randomization

2.5

Stratified block randomization will be used in the study based on the SAS proc plan sentence at the appropriate length. The seed is set as the running time of the program and the case number of the experimental group and the control group is in a ratio of 1:1. The serial number 001-360 which corresponds to a participant will be assigned to each center randomly. Centers are ordered in the alphabetical list by the initial letter of pinyin and offer treatment in increasing sequence.

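### The effective and obvious effective rates are exclusive bands, so patients who improve more drop out of them and the better arm can show the lower rate; define both cumulatively and correct the sign of n

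*Protocol article*

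**What the plan says.** Section 5.1.1 names the modified Barthel index and the simple Fugl–Meyer motor score among the primary outcomes. Section 5.2.1 then states the primary criterion: "The comparison of obvious effective rate and effective rate in improvement degree of motor function and living ability among groups and within groups".

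The same section sorts patients by n, defined as the score before treatment minus the score after, divided by the score before. There are four non-overlapping categories:

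- clinical control: n ≥ 90%
- obvious effective: 70% ≤ n < 90%
- effective: "Effective rate: 70% > n ≥ 30" (per cent)
- ineffective: n < 30%

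No rate that adds categories together is defined, and clinical control is not named in the comparison. Section 5.2.2 uses the same two rates again for Barthel, the western aphasia battery and the water swallow test.

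Section 2.3 (Grouping) sizes the trial on a single rate: "the effective rate of the routine treatment group is 80 percent", and "the morbidity rate of eye-acupuncture and routine treatment group is 90 percent". The second is evidently meant as an effective rate too. The section does not say which scale or which category these rates describe.

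**The concern.** A responder rate should rise whenever more patients do better. These two do not. A patient who moves from 60% to 75% improvement lowers the effective rate. One who reaches 90% is lost to both rates, although that is the best outcome on the scale. An effective treatment that pushes patients up through the bands can therefore leave the effective rate unchanged or reduce it.

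The banded rate also fits poorly with the rate used for the sample size. Taken as the 30 to <70% band, the planning figures would have 90% of the experimental arm improving by less than 70%, with only 10% left for clinical control, obvious effective and ineffective together.

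The formula adds a second fault. Sections 3.3 and 3.4 treat a higher Barthel score as better: below 70 is required for entry, and above 70 is excluded as mild. With before minus after in the numerator, a rise from 40 to 60 gives (40 − 60)/40 = −50%, which falls under ineffective.

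**Working it through.** **1. The plan's own figure.** Inputs from section 2.3: rates 0.80 and 0.90; α "is 0.05 (one side) and" β 0.20. Allocation from section 2.5: "the case number of the experimental group and the control group is in a ratio of 1:1". With pooled variance and no continuity correction, the mean rate is 0.85 and

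n = [1.645·√(2·0.85·0.15) + 0.8416·√(0.80·0.20 + 0.90·0.10)]² / 0.10² = (0.8307 + 0.4208)² / 0.01 = 156.6, so 157.

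This matches "the sample size in both groups is 157". Then 157/0.90 = 174.4, so 175, matching "With an estimated 10 percent dropout rate, the sample size is 175". The arithmetic is sound for one ordinary two-category rate, and power at 157 per arm is 80.1%.

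**2. What the bands do under the planning effect.** Assumptions, since the article gives no SD:

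- n has its sign corrected and is normal with the same SD in both arms.
- P(n ≥ 30%) is 0.80 in control and 0.90 in experimental.

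The arm means are then 30 + SD·0.8416 and 30 + SD·1.2816. The effective band has probability Φ((70 − mean)/SD) − Φ((30 − mean)/SD), and the obvious effective band Φ((90 − mean)/SD) − Φ((70 − mean)/SD). Power in favour of the experimental arm is Φ(difference/SE − 1.645), with SE = √{[p₀(1−p₀) + p₁(1−p₁)]/157}.

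| SD of n (points) | Effective band, control vs experimental | Power | Obvious effective band, control vs experimental | Power |
|---|---|---|---|---|
| 15 | 76.6% vs 81.7% | 30% | 3.3% vs 8.0% | 56% |
| 20 | 67.7% vs 66.4% | 3% | 10.8% vs 19.3% | 69% |
| 25 | 57.6% vs 52.5% | 0.5% | 16.5% vs 24.3% | 54% |
| 30 | 48.9% vs 42.1% | 0.2% | 18.8% vs 24.3% | 32% |
| 50 | 28.3% vs 21.5% | 0.1% | 15.7% vs 15.2% | 4% |

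Example at SD 20: means 46.8 and 55.6. Control: Φ(1.158) − 0.20 = 0.677. Experimental: Φ(0.718) − 0.10 = 0.664. Ten points of patients enter the band from below, but the share above it grows from 80 − 67.7 = 12.3% to 90 − 66.4 = 23.6%, so 11.3 points leave at the top.

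The obvious effective band shows the same fault later. It moves the right way at SD 15 to 30, but by SD 50 it also reverses, because the gain has passed to clinical control.

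**3. The cumulative rate.** If 80% versus 90% is the rate n ≥ 30%, testing that rate is exactly step 1: 157 per arm and 80% power at every SD.

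**4. What a cumulative cut costs against the score.** On a normal scale, 80% versus 90% is a shift of 1.2816 − 0.8416 = 0.44 SD. Comparing means at one-sided 5% and 80% power needs 2·(1.645 + 0.8416)²/0.44² = 63.9, so 64 per arm. The relative efficiency of the cut is 64/157 = 41%, a loss of about 59% of the information. With ANCOVA and an assumed baseline correlation of 0.5, the need falls to 48 per arm.

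**The case against.** The strongest reply has four parts.

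*A responder endpoint is legitimate and the sample size was built on one.* This stands. The fault is in the band definition, not in the use of a rate. A reader might infer that cutting the scores into categories wastes most of the power. The figures do not support that: a cumulative cut keeps the planned 80% at 157 per arm. It loses information, which is a different quantity. The collapse belongs to the exclusive effective band.

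*One of the two named rates usually still moves the right way.* True at SD 15 to 30. However, its power is then 32% to 69%, still short of the plan, and the article gives no rule for the case where the two rates point in opposite directions.

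*The test and covariates are for the analysis plan.* This also stands. A reader might infer that baseline scores and centre will go unused. Section 2.9 lists only analysis sets and fixes no model, so the article does not say so. The bands are different: section 5.2.1 states them outright.

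*The authors may intend a total rate.* Likely, but it is not what is written. Section 5.2.2 does define effectiveness on the TCM symptom score cumulatively, as n ≥ 50%, so the document uses two notions of effective. A reader might go further and say the 80%/90% can only be cumulative. That is too strong: the source studies are not shown, and at SD 15 the band itself holds 76.6% versus 81.7%. Cumulative is the easier reading, and the investigators must confirm it.

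**Conclusion.** The point holds as a defect in the stated primary criterion. Neither rate rises steadily with benefit, patients at n ≥ 90% count in neither, and the effective rate can move against the better arm. Under the planning effect, its power is about 30% at SD 15 and 3% or less from SD 20 upward, against the stated 80%.

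These sizes rest on three assumptions: the 80%/90% are cumulative rates, n is normal with equal SD, and the SD lies in the range shown. The direction of the fault does not depend on them, since it follows from the band limits alone. The sign error needs no assumption for Barthel. It extends to Fugl–Meyer if that motor score also rises with better function.

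**What to change.** 1. In sections 5.2.1 and 5.2.2, define the responder rate once and cumulatively: total effective = n ≥ 30% (clinical control + obvious effective + effective). If a stricter rate is wanted, define obvious effective or better as n ≥ 70%. The four categories can still be tabulated descriptively.
2. For scales where higher is better (Barthel, Fugl–Meyer), use n = (after − before)/before. Without this, the cumulative definition would still count improvers as failures.
3. In section 2.3, state which scale and which definition the 80% and 90% refer to, and correct the word morbidity. If they prove not to be n ≥ 30% rates, the sample size needs to be recalculated.
4. As a cheap addition, also report day-28 Barthel and Fugl–Meyer scores by ANCOVA on baseline score and centre, using data already collected. Making this the primary comparison instead of the rate is the sponsor's choice, and would need a new sample-size justification because the present one rests on a rate.

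Items 1 to 3 are wording changes. If the 80%/90% are confirmed as n ≥ 30% rates, the 157 per arm is unaffected. Item 4 adds a short analysis and no new measurements.

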### Exclusion criteria

3.4

(1)Lacking definitive imaging examination, such as CT or MRI.(2)Special types of stroke: individuals with progressive stroke or intracerebral hemorrhage after cerebral infarction or with disturbance of consciousness.(3)Individuals with mild syndrome; individuals with slight stroke or slight neurological defect and the evaluation of modified Barthel index is more than 70 points; individuals without disability or with rapid improvement of symptoms, such as individuals with the transient ischemic attack (TIA) and (RIND).(4)Individuals who receive treatment of dredging blocking vessels in the acute stage (such as thrombolysis, arterial thrombectomy, super early thrombus aspiration, and stenting).(5)Individuals with bleeding tendency; individuals with serious bleeding within 3 months.(6)Individuals with severe cardiac insufficiency, atrial fibrillation, heart valve disease, or individuals after heart valve replacement.(7)Individuals with other diseases, which can influence the function of limb movement; individuals with limb motor dysfunction caused by claudication, rheumatoid arthritis, or gouty arthritis before treatment.(8)Similar diseases: individuals with CT or MRI imaging of neurological symptoms caused by non-vascular factors; individuals who have suffered from intracranial neurobiology or arteriovenous malformation, aneurysm or neuro-tumor, or individuals with cranial neuro-tumor visible in imaging; individuals with cerebral trauma, multiple sclerosis, cerebral parasites, seizures, hysterical paralysis, or cerebral amyloid angiopathy.(9)Individuals may be exposed to risks or damage by participating in this study from recruitment investigators’ points of view.(10)Disabled individuals (blind, deaf, dumb, mental disorders, mental disorders, and any other limb disability which can affect the evaluation of neurological impairment).(11)Individuals who have known or suspected of having a history of drug or alcohol abuse, or considered inappropriate by the recruitment investigators.(12)Allergic individuals: people who have known or suspected of being allergic to related substances in this study.(13)Individuals who are in other clinical trials or have participated in other drug trials in the past 3 months.

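### The response formula in 5.2.1 has the wrong sign for the modified Barthel index, and for Fugl–Meyer on the usual reading: improvement is classed ineffective, and a loss of 30% or more counts as response

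*Protocol article*

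**What the plan says.** Section 5.1.1 of the protocol article names three primary outcomes: the modified Barthel index, the simple Fugl–Meyer score and resting-state fMRI.

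Section 5.2.1 sets the criterion for the two clinical scales as "The comparison of obvious effective rate and effective rate in improvement degree of motor function and living ability among groups and within groups". It gives one formula, in which n is "points before treatment − points after treatment) ÷ points before treatment] × 100", expressed as a percentage. The classes, with cut-offs in per cent, are clinical control from 90 upwards, then "Obvious effective rate: 90% > n ≥ 70", "Effective rate: 70% > n ≥ 30" and "Ineffective rate: n < 30". fMRI has its own item, a comparison before and after treatment.

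Section 5.2.2 gives a before-minus-after formula for the TCM symptom score with a single 50% cut-off, and ties a positive n to improvement. Its item 3 then calls for obvious effective and effective rates "made by ADL scales (modified Barthel index), WAB and water swallow test", without a further formula.

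The direction of the Barthel index can be read from the eligibility rules. Section 3.3 requires a score below 70. Section 3.4 excludes mild cases, among them those with "slight neurological defect and the evaluation of modified Barthel index is more than 70 points".

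**The concern.** A before-minus-after formula gives a positive value only when the score falls. That suits a symptom score that drops with recovery. Section 5.2.1 applies it to an index on which recovery raises the score, and nothing else in the article reverses the sign, takes an absolute value, re-scores the scale or supplies another formula.

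These classes are the stated criterion for the clinical primary outcomes. Programmed as printed, they would count recovering patients as failures and patients who lose a large share of their baseline function as responders. The between-group comparison of rates would then compare the wrong events.

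**Working it through.** **Inputs.** Formula and cut-offs: 5.2.1. Barthel direction: 3.3 and 3.4. Planning rates: 2.3. A 0–100 Barthel range is an assumption, since the article does not state the maximum; it is needed only for steps 3 and 5.

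**1. The plan's own figure.** Section 2.3 uses rates of 80% and 90%, one-sided α = 0.05 and β = 0.20. With pooled variance and no continuity correction, n per group = [1.645·√(2 × 0.85 × 0.15) + 0.842·√(0.16 + 0.09)]² ÷ 0.10² ≈ 156.6, so 157. Allowing for 10% dropout, 157 ÷ 0.9 = 174.4, so 175. Both stated figures reproduce. The sample-size arithmetic is not at fault; the open question is which response definition those rates refer to.

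**2. Sign.** If after > before > 0, then (before − after) ÷ before < 0. A negative n is below 30%, so the patient is ineffective. For n ≥ 30%, the after-score must be at most 70% of the before-score, that is, a loss of at least 30% of baseline.

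| Barthel before → after | n as printed | Class as printed | n with sign reversed |
|---|---|---|---|
| 40 → 64 | (40 − 64)/40 = −60% | ineffective | +60%, effective |
| 40 → 80 | −100% | ineffective | +100%, clinical control |
| 60 → 40 | +33.3% | effective | −33.3%, ineffective |
| 60 → 18 | (60 − 18)/60 = +70% | obvious effective | −70%, ineffective |

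**3. All eligible integer pairs.** With baseline 1–69 and after-score 0–100, all 4485 of 4485 improving pairs are ineffective; the largest n among them is −1.4% (69 → 70). Of 2415 worsening pairs, 1728 are classed effective or better. These are counts of possible score pairs, not forecasts of patients.

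**4. Baseline 0.** The denominator is 0 and n is undefined.

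**5. Reversing the sign does not settle the denominator.**
- (after − before) ÷ before has a ceiling: from 60 the most possible is (100 − 60)/60 = 66.7%, and from 69 it is (100 − 69)/69 = 44.9%. The obvious effective class (70% and above) is out of reach for both.
- (after − before) ÷ (100 − before) has no such ceiling: 60 → 90 gives 30/40 = 75%.
- The choice changes the class. For 20 → 36, the first gives 16/20 = 80% (obvious effective); the second gives 16/80 = 20% (ineffective).

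**The case against.** The strongest reply is that the intent is plain. Section 5.2.1 speaks of degree of improvement, so the line looks like a formula for a falling score carried over to a rising one, and a sensible analyst would flip the sign. That bears on how likely the harm is, not on whether the text is wrong. It also leaves the denominator open, and step 5 shows that this choice alone can move a patient between classes. In a trial that section 5.5 lists as unblinded, the choice should not be made after data are seen.

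The other objections limit the scope, and they stand:

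- A reader might infer that the whole primary result is inverted. The documents do not support that. fMRI is judged separately, and the abstract also describes outcomes as change from visit 1 to visit 4, which this formula does not touch.
- A reader might infer that effective rates near 0% would replace the planned 80% and 90%. Section 2.3 takes its rates from previous studies and names neither scale nor threshold, so it does not tie them to this formula.
- The article states no direction for Fugl–Meyer, WAB or the water swallow test. For Fugl–Meyer, higher-is-better is a natural reading of a motor function score. For WAB it is an inference, as is the carry-over of the 5.2.1 formula, which rests on the shared class labels in 5.2.2. For the water swallow test the document does not show whether the present formula fits.

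**Conclusion.** Wrong as written. For the modified Barthel index this rests on the protocol's own text and simple algebra: every improvement from a baseline above 0 is ineffective, and every loss of 30% or more is effective or better. For the simple Fugl–Meyer score the result is the same, on the assumption that higher is better. For WAB it appears to be the same. The fMRI outcome and the sample-size arithmetic are unaffected.

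It should be corrected before analysis because it is the stated response rule for two of the three primary outcomes. The damage arises if the line is applied literally, or if it is repaired informally after the data are known.

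**What to change.** In 5.2.1, and in 5.2.2 wherever the same classes are used, state the direction and the formula for each scale before analysis.

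- For scales where higher is better, use after − before in the numerator.
- Fix the denominator in advance. Baseline stays closest to the present form, but it is undefined at baseline 0 and caps n (66.7% from a baseline of 60 on an assumed 0–100 scale). Scale maximum − before is an option that removes the cap, but it changes what the 30/70/90% cut-offs mean and is undefined when baseline equals the maximum, as could happen on WAB in a patient without aphasia.
- State how the undefined cases are classified.
- Keep before − after only for scores that fall with recovery, such as the TCM syndrome score, and state the direction of the water swallow test.
- Confirm that the 80% and 90% rates in 2.3 use the corrected definition. If they do not, the basis of the sample size needs to be revisited.

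The cost is a small text change in the protocol, carried into any analysis plan, and a check of the planning rates against their sources. No new data are needed.
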